While the rollout of RDTs at clinic level has some evidence base (in part, from the previous ACTc studies), there is little available data on the effectiveness with which this intervention can be provided at community level through CHWs. The data that does exist locally is based on two studies, one conducted in 2006^[[1]](#footnote-1)^ and one ongoing pilot programme^[[2]](#footnote-2)^. Evidence from the study and from the pilot programme suggests that RDTs are not utilised effectively by CHWs. In the study, high rates of invalid tests were reported due to user error, and in both programmes, RDTs are incorrectly applied to patient’s symptoms. The results are that very large numbers of RDTs are used, and very few cases of malaria are adequately detected. The effect of RDTs on treatment decisions and accuracy was not noted by either study.

Use of RDTs at community level will also have an effect on current guidelines for management of febrile illness and diseases of children. The current community IMCI guidelines for Afghanistan (and most of Asia) do not include RDTs in the differential diagnosis of childhood diseases in the community. The current guidelines favour a blanket approach to treatment of “suspected malaria” where there is no other obvious cause of illness and the patient is in an endemic area. Changing these guidelines requires an evidence based approach to assess both the clinical and economic aspects of the intervention – something which has thus far not been conducted despite the trend in programming which has now started to deploy RDTs much more widely.

This study aims to provide evidence on the effectiveness of RDTs that have been deployed at community level by measuring the accuracy of the tests themselves, and the accuracy with which treatment is provided to malaria positive and malaria negative cases.

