### Trial Arms:

**Phase I:**

*Arm 1: Non-intervention arm:*

The non-intervention arm will be based on the existing clinical diagnosis, pre-referral treatment and referral to a clinic in areas where RDTs have not been deployed at CHW level. Arm 1 CHWs will receive refresher training according to the National Strategy for CBMM which includes the current IMCI guidelines.

Vs:

*Arm 2: RDT Arm*

Provision of community level diagnostics by rolling out RDTs to CHWs through the national strategy for Community based Management of Malaria. The arm has been designed exactly as the current National guidelines for RDT implementation..The arm will include:

- Clinic level microscopy or RDT and CHWs using RDTs to provide parasitological diagnosis to diagnose, treat and/or refer patients. Under this scheme, CHWs will be provided with CQ, SP and artesunate (AS). Depending on the diagnostic result, they prescribe according to the National Treatment Guidelines (CQ for confirmed vivax, SP and AS for confirmed falciparum, and no antimalarial for a negative result).
- CHW training will be conducted exactly as described in the CBMM strategy, using a “trickle down approach” where Training of Trainers takes place at the central level for provincial trainers of local NGOS who run the health service. These, in turn, run workshops for training CHSs and CHWs (see section 2.2 for pre-evaluation of training and roll-out). Participants will receive training to enforce revised IMCI guidelines, taken from the CBMM strategy document, which include an RDT in the algorithm for fever (see annex 2).
- There are no plans for additional support or refresher training, and no plans for quality control and assurance contained in the National Plan.
- CHWs are not equipped with suitable storage facilities for the RDTs, for example evaporative coolers.
- Monitoring and evaluation takes place according to the draft strategy.

The second phase of the trial will be initiated in Feb 2012. The second phase of the trial will re-randomise clinics to either the RDT arm (as in arm 2, above) and a third arm (arm 3). The third arm will answer the question: “how can the performance of RDTs at community level be enhanced?”. The same set of outcomes will be used to measure the relative effectiveness of each approach. A revised random allocation using the same methods will be conducted for the Phase II randomisation.

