### Trial Secondary Outcomes:

- % of Pf cases treated with ACT.
- % of patients <10 years of age who are correctly treated (estimated at 40% of all patients)
- % of malaria negative patients receiving antimalarial drug
- % of malaria negative patients receiving antibiotics
- % of patients treated per policy

Per policy defined as:

- Suspected malaria which is PCR confirmed treated with CQ/SP
- Community based diagnosed Pf, subsequently confirmed as Pf treated with SP/AS
- Community based diagnosed Pv, subsequently confirmed as Pv treated with CQ
- No antimalarial given to negative cases (confirmed by PCR)
- Proportion of patients incorrectly treated in each arm, including data collected at the clinic level.
- Time to first treatment from onset of symptoms.
- Cost per patient correctly treated.
- Cost per patient treated per policy.
- Invalid rate, specificity and sensitivity of RDTs deployed at community level (against PCR).
- Number of patients attended by CHWs and type of attendance.
- Number and proportion of patients successfully referred by CHWs to BHCs.
- Proportion of malaria negative and positive given antibiotics at CHW and/or clinic level.

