### Risks and potential adverse events:

There are minimal risks associated with this study. Blood samples would, in most cases, be taken anyway for the application of the RDT is associated with minimal risk of secondary infection at the puncture site and with mild pain.

The main risk is in the mistreatment of falciparum malaria with either no antimalarial or with an ineffective antimalarial (i.e. CQ). Currently, falciparum malaria is quite rare in the study areas (although it may vary seasonally and geographically) so the risk of this occurrence is low. According to the National Guidelines and the study protocol, all Pf positive patients will be referred to a clinic for further evaluation which further reduces the risk of this occurring, since all clinics will have parasitological diagnosis available (either through RDT or through microscopy).

The trial intervention arm is unlikely to increase this risk, in fact, rather the opposite. This potential adverse event will be monitored throughout the trial and its occurrence will be reported to the Data Safety and Monitoring Board (DSMB). Immediately following a PCR result which is positive for Pf (regardless of coinfection), results from the patient record form will be cross checked to see which treatment was given. Because of logistical constraints, PCR results will not be known for more than 2 weeks after the initial assessment of the patient. Every effort will be made to trace the patient and ensure that they have recovered. If not, they will be referred to the health facility for further treatment.

Depending on the frequency with which this event occurs, the study staff will inform the DSMB of any action being taken which could include re-training of staff or withdrawal of CHWs from the trial. All efforts will be made to follow-up the patient within a few days of knowing the PCR result. All patients will be advised by CHWs to seek treatment at the clinic if symptoms recur or continue following the treatment.

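### The treated-per-policy outcome is scored against a PCR result the CHW cannot see, so it partly marks policy-following as off policy and nearly repeats the primary outcome

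*Protocol*

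**What the plan says.** Section 2.6.2 of the protocol lists the percentage treated per policy as a secondary outcome, and a cost outcome uses the same count. The definition has four lines. The first, for patients treated on suspicion, is "Suspected malaria which is PCR confirmed treated with CQ/SP". The second deals with falciparum found by the CHW and counts it only when the species is borne out later: "Community based diagnosed Pf, subsequently confirmed as Pf treated with SP/AS". The third sets the same condition for vivax and chloroquine. The fourth, for patients without malaria, is "No antimalarial given to negative cases (confirmed by PCR", so negative status is also set by the laboratory.

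The policies being scored are described elsewhere. Section 2.5.1 bases Arm 1 on existing clinical diagnosis, treatment before referral, and referral, with refresher training that includes the current IMCI guidelines. Section 1.2 says of those guidelines: "The current guidelines favour a blanket approach to treatment of “suspected malaria” where there is no other obvious cause of illness". It restricts this further to endemic areas. For CHWs with RDTs, section 2.5.1 says "Depending on the diagnostic result, they prescribe according to the National Treatment Guidelines". On timing, section 2.10.3 states that "PCR results will not be known for more than 2 weeks after the initial assessment of the patient".

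**The concern.** Whether a CHW followed policy can only be judged on what the CHW had at the consultation. Here every line needs a laboratory result that arrives weeks later. Two kinds of policy-following conduct are then counted as breaches: presumptive treatment of an Arm 1 patient who proves PCR-negative, and action on an RDT result that PCR later contradicts.

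Two things are at stake. A Phase I difference between arms on this outcome, or on its cost derivative, could be read as a difference in compliance when part of it comes from the definition. And the outcome cannot separate prescriber behaviour, which section 1.2 says has to change and which Arm 3 is built to improve, from test error. Correct treatment against PCR is already the primary outcome (section 2.6.1), so a second outcome on nearly the same basis adds little.

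**Working it through.** The protocol gives no expected value for this outcome, so there is no figure to reproduce. I applied the four lines to CHWs who follow their arm's policy fully.

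**Inputs**
- PCR positivity among enrolled patients, *p*: not given. Section 1.2 calls malaria a minority cause of febrile illness. Assumed 5–30%.
- RDT sensitivity (Se) and specificity (Sp): section 2.9.1 states accuracy above 95%. Assumed 95% for each, with species read correctly.
- Share of suspected Arm 1 patients the policy would treat, *f*: not given. Taken as the same in PCR-positive and PCR-negative patients, with treatment by the drugs named in the first line.

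**Scores for policy-following conduct**

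| Arm | Situation | Action under the arm's policy | Score as written |
| --- | --- | --- | --- |
| 1 | Suspected, treated presumptively, PCR-negative | Followed | Off policy |
| 2/3 | RDT positive, treated, PCR-negative | Followed | Off policy |
| 2/3 | RDT negative, not treated, PCR-positive | Followed | Off policy |

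The converse also holds: a CHW who withholds treatment despite a false-positive RDT is scored per policy.

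**Arms 2 and 3, full adherence.** Score = *p*·Se + (1 − *p*)·Sp. With Se = Sp = 0.95 this is 0.95 for any *p*, so 5% of adherent consultations are mis-scored. It is more if field accuracy is lower: with Se 0.70, Sp 0.95 and *p* 0.16 (all assumed), 0.16 × 0.30 + 0.84 × 0.05 = 0.09.

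**Arm 1, full adherence.** Treated patients score only if PCR-positive, and untreated patients only if PCR-negative, so score = *f*·*p* + (1 − *f*)(1 − *p*).

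| *f* | Score at *p* = 5% | Score at *p* = 30% | Gap to 95% in Arm 2 (points) |
| --- | --- | --- | --- |
| 1.0 | 5% | 30% | 90 to 65 |
| 0.9 | 0.045 + 0.095 = 14% | 0.27 + 0.07 = 34% | 81 to 61 |
| 0.5 | 50% | 50% | 45 |

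Scored on what was known at the consultation, a fully adherent CHW would get 100% in any arm.

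**Overlap with the primary outcome.** For PCR-negative patients the two definitions are the same: no antimalarial. They can differ only among PCR-positives, so they agree on at least 1 − *p* of patients, which is 70–95% here. One clear difference is that the first line also credits falciparum treated with CQ/SP, and section 1.2 puts falciparum at only about 5–10% of malaria cases.

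**The case against.** The main objection is to size, and it stands. The top row of the Arm 1 table needs a policy of treating every suspected patient, and the protocol does not state one. Section 1.2 limits the blanket approach to endemic areas with no other obvious cause, and describes it within community guidelines for childhood illness. Section 2.8.1 assumes that only 40% of patients are under 10. Section 2.5.1 includes referral in Arm 1, and section 2.5.7 enrols patients who are only referred. Some untreated PCR-negative patients are therefore on policy and are scored so.

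Two stronger readings fail for the same reason. A reader might infer that the definition reverses Arm 1 policy; the documents do not support that. A reader might also take the planned 90% of Arm 1 negatives treated (section 2.8.1) as 90% following policy. That figure is an expected treatment rate based on clinic data, and says nothing about who was on policy.

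The Arm 2 and 3 error is small if field accuracy is near the stated figure. In Phase II both arms use RDTs, so much of it should cancel, though Arm 3 adds coolers and quality control that could change test accuracy itself.

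It can also be said that section 2.7.1 declares PCR as the reference for outcomes, that the protocol never calls this outcome adherence, and that behaviour and test error are partly separated elsewhere. RDT accuracy is its own outcome, section 2.9.3 double-reads the tests, and Annex 3 has indicators for treatment of RDT-confirmed cases. This does not remove the point. A general PCR reference suits correct treatment but not conformity with a policy that does not use PCR. The investigators' notes in Annex 3 replace the RDT-confirmed denominators with suspected and PCR-confirmed cases. And listing the two cost outcomes separately implies that two different quantities were meant.

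**Conclusion.** The definition does not measure whether patients were treated according to their arm's policy, and it should be changed. The direction in Phase I is clear: when fully followed, presumptive treatment loses credit for every PCR-negative patient treated, while RDT-guided treatment loses credit only where the test errs.

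The size in Arms 2 and 3 is about 5% at an assumed 95% sensitivity and specificity. In Arm 1 it cannot be fixed from the protocol. A gap of 65–90 points to Arm 2 is the upper bound at an assumed positivity of 5–30%, reached only if the policy treats every suspected patient, and it shrinks as that share falls. This is a should-fix matter for one secondary outcome and its cost derivative. The primary outcome, the randomisation and data collection are untouched.

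**What to change.** Define treated per policy on the information available at the consultation, whatever PCR later shows.

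- **Arms 2 and 3:** score agreement between the RDT result on the CHW form and the recorded action, under the policy already stated in section 2.5.1.
- **Arm 1:** score the recorded action against the CHW's recorded clinical diagnosis, under the guideline used for Arm 1 training. Sections 1.2, 2.5.1 and 2.6.2 must first be reconciled on what that policy is, including when referral counts as following it.
- **PCR:** keep it for correct treatment.
- **Cost-per-policy outcome:** use the revised definition.

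No new data are needed: section 2.7.2 says the form records the diagnosis, whether an RDT was used and its result, and the action taken. For Arms 2 and 3 the cost is a rewording. Arm 1 takes somewhat more work, because section 2.5.1 gives no scorable rule and one has to be written from the guideline.

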### Evaluation Criteria:

The evaluation criteria will follow that of the draft Community Based Management of Malaria guidelines. These represent national targets for inputs, outputs and outcome indicators with targets set by the National Programme and its partners.

Key indicators for the evaluation are laid out in the draft CMM strategy. At the time of writing this is still in draft and so these indicators and the outcome measures may change.

The key indicators and targets to monitor inputs, process and outcome of CBMM programme (taken from the Draft CMM Strategy for Afghanistan) are shown in annex 3.

## Outcome Measurement and Recording:

### Outcome Measurement:

In the community healthcare setting, there are several possible outcomes to any consultation with a CHW. Once the initial consultation is made, the CHW will decide on a diagnosis and then a specific course of action. In addition, patients may present at the clinic, either after a consultation with a CHW, or without a consultation. In the former case, the patient may have been referred, or may have self referred. The patient may also attend the clinic without having a consultation with a CHW (figure 3).

**Figure 3: Schematic diagram showing the potential path of a patient through the health system, starting at community level,**

Data and outcomes will be recorded at both the clinic and community level. The outcomes will be measured against PCR based diagnosis of malaria (including Pf, Pv, *P ovale* and *P malariae*). Filter paper blood spots will be collected at the diagnosis stage (at community and clinic level).

### Data recording:

Patient data will be recorded on pro-forma Patient Tracking Forms designed for each level of the study health system (i.e. CHW and clinic level).

The CHW record form is designed for semi-literate health-workers and uses both pictorial and textual components. All health workers will be trained by study staff (registrars) in filling out the form. The form will have been pretested and validated prior to commencement of the trial. The form will record the patients age and sex, symptoms (fever, cough, diarrhoea, shivering/rigors), length of time since symptoms began, diagnosis made (including whether an RDT was used and what the result was), and then the action taken, as in Figure 2. See annex 4).

For clinics, the form employed in the randomised trial has been adapted for use (see annex 5). The clinic physician (whether a doctor or not) will record the information at the time of the consultation.

Whether referred by CHWs or not, patients will be given an identifier card to present to the clinic to indicate that they were enrolled in the study. The referral note will have the same patient number as the enrolment data, which will be used to match the patient at the clinic with the same patient enrolled by the CHW.

## Sample Size and Statistical Methods:

### Sample Size Assumptions:

Key parameters and assumptions used to calculate the sample size are listed below:

- Number of clusters (clinics): 22
- Number of Health Posts: 207
- Number of CHWs: 414
- Expected difference in primary outcome in Phase 1 (40%):
  - Arm 1 - Non-intervention: 10% correctly treated vs.*
  - Arm 2 – RDT: 50% correctly treated*
- Expected difference in major secondary outcome (in phase 1):
  - Proportion of Pf positive patients receiving ACT: 0.5% in arm 1 vs. 50% in arm 2.*
  - Proportion of malaria negative patients treated with antimalarial: 90% in arm 1 vs. 50% in arm 2*
  - Proportion of malaria negative patients treated with antibiotic: 5% in non-intervention arm, 15% in RDT arm.
- Expected difference in primary outcome in Phase 2 (20%):
  - Arm 2 – RDT: 50% correctly treated.
  - Arm 3 – RDT extended programme: 70% or greater are correctly treated.
- Expected differences in major secondary outcome (in phase 2):
  - Proportion of Pf positive patients receiving ACT: 50% in arm 2 vs. 85% in arm 3.
  - Proportion of malaria negative patients treated with anti-malarial: 50% in RDT arm, 25% in RDT extended programme arm.
  - Proportion of malaria negative patients treated with antibiotic: 15 % in RDT arm, 20% in RDT extended arm.
- Sub-group analysis assumes that 40% of patients are under 10yrs*.

* estimates are based on initial results from the current randomised trial, based on data from 22 clinics in Afghanistan. There are no estimates in this region for effectiveness at CHW level.

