### Balance criteria:

The following variables that are expected to be important correlates of the primary outcome and on which we wish to achieve balance were based on a data collected in 2009 in the same study clusters and over the same study period i.e. July to December.

1. Harmonic mean. For a given number of clusters and overall sample size maximum statistical efficiency is obtained if an equal number of patients per cluster are selected. The total sample size of 1500 across 22 clusters would require an *arithmetic* mean of 68 patients per cluster. However, due to the huge variability in the proportion of patients seen with suspected diarrhoea, URTI and malaria (when CHWs are likely to use RDTs) per cluster this approach was not seen as appropriate for several reasons including time to reach sample size quota, and cluster representation. Hence the sample size was weighted according to the cluster proportion of patients seen with suspected diarrhoea, URTI and malaria to achieve a *harmonic* mean of 68 patients per cluster in each arm. Since the sample size calculation was done before randomisation the overall harmonic mean (for all clusters) was used but this does not guarantee a harmonic mean of 68 per arm and therefore this was included as a restriction factor in the randomisation.
2. Total sample size. The precision and power of a study are usually maximised when sample sizes are similar in the treatment arms. In CRTs this means that the number of clusters as well as the number of individuals should be similar across treatment arms. Therefore, due to the variability in sample size per cluster this was also added as a restriction factor.
3. Number of health posts. There is a substantial amount of variation in the number of health posts per cluster from 2 to 26. Clusters (clinics) with bigger catchment populations have more health posts and therefore by balancing on this factor and equal sample size per arm will be achieved.

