### Number of consultations per clinic and health post:

In the 22 study clinic, there are 207 health posts (414 community health workers). The sample size will be limited by the number of consultations where an RDT will be deployed. The table shows the monthly activities report for the Health Posts in the study clinics for 3 months, from July-Sept 2010.

| **Province/clinic** | **Number of Health Posts** | **Number of treatments given for:** | | | |
| --- | --- | --- | --- | --- | --- |
|  |  | **Malaria** | **URTI** | **Diarrhoea** | **Total** |
| **Kunduz** | **65** | **47** | **2693** | **3161** | **5901** |
| Ajighan | 6 | 3 | 267 | 345 | 615 |
| AngorBagh | 7 | 3 | 568 | 823 | 1394 |
| ArbabRamazani | 2 | 2 | 54 | 73 | 129 |
| BolaQachi | 5 | 10 | 246 | 268 | 524 |
| CharSari | 6 | 2 | 245 | 205 | 452 |
| Khan Abad | 20 | 0 | 560 | 584 | 1144 |
| KhwajaGhaltan | 8 | 6 | 264 | 387 | 657 |
| Madrasa | 3 | 17 | 131 | 103 | 251 |
| Nick Pay | 3 | 0 | 36 | 49 | 85 |
| SandoqSai | 5 | 4 | 322 | 324 | 650 |
|  |  |  |  |  |  |
| **Nangarhar** | **142** | **2471** | **3736** | **3611** | **9818** |
| Baro | 8 | 63 | 158 | 230 | 451 |
| Batikot | 21 | 450 | 541 | 468 | 1459 |
| Behsood | 16 | 216 | 354 | 297 | 867 |
| Chardhi | 6 | 45 | 112 | 93 | 250 |
| GardiGhos | 6 | 310 | 342 | 281 | 933 |
| Khewa | 12 | 158 | 487 | 670 | 1315 |
| LandaBuch | 10 | 174 | 258 | 247 | 679 |
| MamandDara | 11 | 382 | 319 | 313 | 1014 |
| NajmulQura | 6 | 189 | 291 | 329 | 809 |
| Rodat | 13 | 52 | 50 | 37 | 139 |
| SangarSarai | 18 | 212 | 271 | 338 | 821 |
| Shegay | 15 | 220 | 553 | 308 | 1081 |
| **Grand Total** | **207** | **2518** | **6429** | **6772** | **15719** |

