### Sample size:

An initial sample size of 1500 was selected for phase I to assess the secondary outcome of number of malaria positive patients correctly treated. Because Pf malaria is rare, the study is not powered for assessing the proportion of Pf cases correctly treated, although this will be examined as an exploratory analysis. For Phase II an initial sample size of 4000 individuals would assess the same secondary outcome, adjusted for cluster sampling. The confidence level (alpha) is 0.05 and the power (beta) is 0.8.

The sample size for both phases is adjusted for both intra-cluster variation (intra-cluster correlation coefficient of 0.5). To give a harmonic mean (see section 2.5.3) of 68 patients per cluster for phase I and 182 for phase II sample sizes of 2542 and 6792 are required in phase I and phase II respectively. This step is discussed in more detail in section 2.5.3.

|  |  | **Phase I** | | **Phase II** | |
| --- | --- | --- | --- | --- | --- |
| **Clinic** | **Province** | **SS weighting by cluster size** | **SS Weighted by cluster size for harmonic mean of 68** | **SS weighting by cluster size** | **SS Weighted by cluster size for harmonic mean of 182** |
| Ajighan | KDZ | 73 | 124 | 194 | 330 |
| AngorBagh | KDZ | 163 | 276 | 435 | 739 |
| ArbabRamazani | KDZ | 15 | 25 | 41 | 70 |
| BolaQachi | KDZ | 66 | 112 | 175 | 297 |
| CharSari | KDZ | 52 | 88 | 138 | 234 |
| Khan Abad | KDZ | 147 | 249 | 392 | 666 |
| KhwajaGhaltan | KDZ | 66 | 112 | 176 | 299 |
| Madrasa | KDZ | 30 | 51 | 80 | 136 |
| Nick Pay | KDZ | 12 | 20 | 33 | 56 |
| SandoqSai | KDZ | 63 | 107 | 169 | 287 |
| Baro | NGR | 37 | 63 | 100 | 170 |
| Batikot | NGR | 121 | 205 | 322 | 547 |
| Behsood | NGR | 72 | 122 | 191 | 324 |
| Chardhi | NGR | 21 | 36 | 55 | 93 |
| GardiGhos | NGR | 77 | 130 | 206 | 350 |
| Khewa | NGR | 109 | 185 | 290 | 493 |
| LandaBuch | NGR | 56 | 95 | 150 | 255 |
| MamandDara | NGR | 84 | 142 | 224 | 380 |
| NajmulQura | NGR | 67 | 114 | 178 | 302 |
| Rodat | NGR | 12 | 20 | 31 | 53 |
| SangarSarai | NGR | 68 | 115 | 181 | 307 |
| Shegay | NGR | 89 | 151 | 238 | 404 |
| Sample Size | | 1500 | 2542 | 3999 | 6792 |
|  |  |  |  |  |  |
| Arithmetic Mean | | 68.1818182 | 115.5455 | 181.7727273 | 308.7273 |
| Harmonic Mean | | 40.1240439 | 67.61738 | 107.1515805 | 182.1944 |
| Ratio (arithmetic:harmonic) | | 1.69474 |  | 1.69853 |  |

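### The clinic-derived control rate in 2.8.1 is not reconciled with the CHW treatment counts or the Kunduz quotas; planned by province, the pooled Phase I difference may be about 12 to 16 points, not 40

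*Protocol*

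**What the plan says.** Protocol 2.8.1 lists among its sizing inputs "Arm 1 - Non-intervention: 10% correctly treated vs" and "Arm 2 – RDT: 50% correctly treated", together with "Proportion of malaria negative patients treated with antimalarial: 90% in arm 1 vs. 50% in arm 2". The footnote to these values says "estimates are based on initial results from the current randomised trial, based on data from 22 clinics in Afghanistan" and adds "There are no estimates in this region for effectiveness at CHW level".

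Protocol 2.8.2 says "The sample size will be limited by the number of consultations where an RDT will be deployed" and tabulates CHW treatments for malaria, URTI and diarrhoea at the same health posts for July to September 2010. On the quotas, 2.5.3 states that "the sample size was weighted according to the cluster proportion of patients seen with suspected diarrhoea, URTI and malaria".

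Eligibility (2.5.7) is narrower than that base. A patient enters only if the CHW or clinician considers malaria, shown by an antimalarial, a test that would be asked for, or referral for malaria diagnosis. Under 2.6.1, a PCR-negative patient given no antimalarial is correctly treated.

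Protocol 2.8.3 uses an intra-cluster correlation (ICC) of 0.5 and says "The confidence level (alpha) is 0.05 and the power (beta) is 0.8". It ties the initial 1,500 to a secondary outcome in malaria-positive patients, and raises it to 2,542 to reach the harmonic mean.

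**The concern.** The Arm 1 value describes clinic prescribers, while the control condition is CHW practice. The protocol discloses the source, but the next subsection prints CHW data from the trial's own health posts and never sets them against the assumed value. In Kunduz those data show very little treatment for malaria, so an RDT would have little overtreatment to remove there.

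Two things are at stake. The 40-point planning difference may hold in only one of the two provinces. And a weak pooled result could be read as failure of RDTs to improve targeting, although the effect could appear mainly in Nangarhar.

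**Working it through.** **1. The plan's own figures.** Adding the 2.8.3 quotas over the Table 2 allocation gives 644 (Kunduz) + 636 (Nangarhar) = 1,280 for Arm 1, and 520 + 742 = 1,262 for Arm 2. The harmonic means are 66.03 and 69.28. All match Table 4. The 1,500 does not reproduce from 10% vs 50%: 20 per arm (two-sided 0.05, power 0.80) × design effect 1 + (68 − 1) × 0.5 = 34.5 gives 2 × 20 × 34.5 = 1,380.

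**2. Kunduz, Arm 1.**
- Malaria treatments (2.8.2): Ajighan 3 + AngorBagh 3 + ArbabRamazani 2 + KhwajaGhaltan 6 + SandoqSai 4 = 18, of 3,445 treatments (0.5%).
- Quotas (2.8.3): 124 + 276 + 25 + 112 + 107 = 644, which is 644/1,280 = 50.3% of Arm 1.
- If nearly all are malaria-negative, 90% treated means 0.9 × 644 ≈ 580. That is 580/18 ≈ 32 times the recorded quarter. Over two quarters (July to December, the study period named in 2.5.3) it is 580/36 ≈ 16 times.
- At recorded volume, at most 18/644 = 2.8% to 36/644 = 5.6% receive an antimalarial.

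**3. Nangarhar, Arm 1.** Treatments are 63 + 216 + 158 + 174 + 52 + 220 = 883 in the quarter, against a quota of 636. A 90% rate is numerically possible.

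**4. Pooled rates.** Assume that quotas fill, that every recorded malaria treatment falls in an enrolled patient, that Kunduz use stays at the recorded level in both arms, that untreated patients are PCR-negative, and that Nangarhar is 10% vs 50%. Kunduz Arm 2 recorded 29 treatments against 520.

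| | One quarter | Two quarters |
|---|---|---|
| Kunduz correct, Arm 1 / Arm 2 | 97.2% / 94.4% | 94.4% / 88.8% |
| Arm 1 = (644 × Kunduz + 636 × 0.10)/1,280 | 53.9% | 52.5% |
| Arm 2 = (520 × Kunduz + 742 × 0.50)/1,262 | 68.3% | 66.0% |
| Difference by patient | 14.4 points | 13.5 points |
| Cluster means, (5 × Kunduz + 6 × Nangarhar)/11 | 49.6% vs 70.2% | 48.4% vs 67.7% |
| Difference of cluster means | 20.6 points | 19.3 points |

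Letting the two arms take different ends of the range widens this to about 12–16 points by patient and 18–22 on cluster means.

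**5. Power** (normal approximation, unpooled variance, two-sided 0.05, ICC 0.5, 68 per clinic).
- 10% vs 50% throughout: effective n = 11 × 68/34.5 = 21.7 per arm; SE = √[(0.09 + 0.25)/21.7] = 0.125; 0.40/0.125 = 3.19; power about 89%. A pooled-variance form gives about 85%.
- Unstratified, 52.5% vs 66.0%: SE = √[(0.249 + 0.224)/21.7] = 0.148; 0.135/0.148 = 0.92; power about 15%. 53.9% vs 68.3% gives about 17%. Over the wider range, power is about 13–19%.
- Nangarhar alone, 6 clinics per arm: SE = √[0.34 × 34.5/(68 × 6)] = 0.170; 0.40/0.170 = 2.36; power about 66%.
- Province-stratified on clusters, weights 5/11 and 6/11, ICC 0.5 within province: two quarters, 5/11 × (−0.056) + 6/11 × 0.40 = 0.193, power about 43%; one quarter, 0.206, about 53%. Over the wider range, power is about 40–56%.

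**The case against.** The best defence is that the CHW table measures something else. It counts treatments recorded under malaria, URTI or diarrhoea, not antimalarials among patients in whom malaria was considered. It holds no suspected cases, referrals or PCR results, so it cannot yield a correct-treatment rate, and the statement that no CHW estimate exists is not false. This stands. A reader might infer that 10% correct cannot occur in Kunduz; the documents do not show that. If Kunduz enrols almost only patients who get an antimalarial, the rate could hold, but the quota would then go unfilled at recorded volumes.

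The other escapes are weaker:
- Patients entering by a would-be test or referral need not receive an antimalarial, and count as correct if negative.
- If untreated patients were incorrect because they were positive, 10% correct with 36 treated would need at least 644 − 36 − 64 = 544 of 644 (84%) to be untreated positives. The Scientific Rationale calls vivax, the main species, a minority cause of febrile illness.
- If the table held monthly figures, six months would give 108/644 = 17%, still far from 90%.
- Practice may shift with refresher training, but nothing in the protocol argues for a 16- to 32-fold rise.

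A reader might also infer that the 40 points are lost everywhere, or that Arm 1 at about 52% already equals Arm 2's 50%. Neither follows. Nangarhar can still show 40 points. The second reading moves Kunduz in Arm 1 only, so RDTs there would have to lower correct treatment from about 94% to 50%.

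Finally, 2.8.3 ties the 1,500 to a secondary outcome, so no error in that total is shown. Detailed analysis by province may properly sit in the analysis plan that 2.8.4 announces; its absence here is not the defect.

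**Conclusion.** The point holds as a failure to reconcile. At recorded CHW activity, the Arm 1 planning value and the Kunduz quotas cannot both be met. Either half of Arm 1's quota is at risk, because it was set on URTI and diarrhoea volume that eligibility does not follow, or most Kunduz controls will be untreated and largely correct.

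In the second case, the planned 40-point contrast shrinks to about 12–16 points by patient, or 18–22 on cluster means. Stratifying by province recovers much of the lost power, but not the 0.8 stated in 2.8.3. The unstratified power figures also understate what the design can do, because randomisation was stratified by province.

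These sizes rest on 2010 volumes, unchanged Kunduz practice in both arms, PCR-negative untreated patients, and the planned rates in Nangarhar. They show what the protocol's own figures imply; they are not a forecast. The matter carries into Phase II, which reuses 50% for Arm 2 and draws 3,114 of its 6,792 quota from Kunduz.

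**What to change.** - Reconcile the Kunduz quotas in 2.8.3 with the eligibility rule in 2.5.7 and the counts in 2.8.2. Say whether the quotas are expected to fill, and with which patients.
- Replace the single 10% and 50% in 2.8.1 with planning rates by province, and state their sources and assumptions.
- Restate the expected pooled Phase I difference and its power as a range at the stated ICC.
- Specify that the primary outcome is analysed stratified by province, using the existing randomisation strata, and reported for each province.
- Before Phase II is fixed, update its 50% comparator from the Phase I Arm 2 result by province.

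The cost is a rewrite of 2.8.1 and 2.8.3 and one stratified analysis, with no extra patients. The drawback is that the stated difference and power become less favourable.
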